#### 2^nd^ randomization

The sample size is based on hypothesized QoL differences (mean difference of 5.7) between the intervention arms based on the landmark Basch et al. study, as well as the unpublished standard deviation of 15.6 for EQ-5D-5L scores from our ongoing SABR-COMET-3 study to capture expected standard deviation for our patient population [13, 14]. Group sample sizes of 125 and 125 will provide 80% power to detect a significant difference based on an alpha of 0.05. We will plan an analysis of Arm A and B after 250 patients.

The total sample size for this trial is 598 based on the primary objective of the first randomization.

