In a study by Basch et al., changes in QoL in patients receiving outpatient chemotherapy for advanced solid tumours were compared [13]. Patients were randomly assigned to complete symptom monitoring electronically, or received standard of care, and results in this systemic therapy population showed a greater improvement in QoL and OS from baseline to 6 months in the symptom monitoring arm. Our study will implement similar methodology in the radiotherapy setting. We will examine differences in patient-reported QoL in the second randomization, comparing change in EQ-5D-5L scores between those who complete questionnaires alone and those who complete questionnaires, a symptom-specific survey and receive HCP-guided intervention.

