### 2nd Randomization (BC Cancer sites only)

#### Primary endpoint

##### Differences in patient reported QoL

As measured by the EQ-5D-5L based on presence or absence of HCP intervention (guided by symptoms reported in the generic radiation-related symptom questionnaire).

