#### 2^nd^ randomization

The 2^nd^ randomization of the study will also employ a 1:1 randomization between Arm A and Arm B, with stratification by sex (female vs. male vs. other).

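### The second randomization's EQ-5D-5L outcome is called a change in the Background but sized as a score; fix one baseline-adjusted outcome and say which SD 15.6 is

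*Protocol article*

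**What the plan says.** Four places in the protocol article bear on the primary outcome of the second randomization.

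- **Background.** The trial's own comparison is described as "comparing change in EQ-5D-5L scores between those who complete questionnaires alone and those who complete questionnaires, a symptom-specific survey and receive HCP-guided intervention". The sentences just before it describe the cited symptom-monitoring study as finding greater improvement from baseline to 6 months.
- **2nd Randomization (BC Cancer sites only), Primary endpoint.** The outcome is a difference in patient-reported QoL, "As measured by the EQ-5D-5L based on presence or absence of HCP intervention". Neither change from baseline nor a time point is named.
- **Sample size calculation, 2nd randomization.** "The sample size is based on hypothesized QoL differences (mean difference of 5.7) between the intervention arms", with the 5.7 credited to the symptom-monitoring study. The SD is "the unpublished standard deviation of 15.6 for EQ-5D-5L scores from our ongoing SABR-COMET-3 study to capture expected standard deviation for our patient population". The result is: "Group sample sizes of 125 and 125 will provide 80% power to detect a significant difference based on an alpha of 0.05".
- **Statistical considerations, Primary endpoints.** The outcome is again QoL measured by the EQ-5D-5L, without mention of change.

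No section gives a baseline/follow-up correlation, an SD labelled as that of a change, a dropout allowance, or the sidedness of the 0.05.

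**The concern.** A follow-up score and a change from baseline are different variables. Randomization gives them the same expected between-arm difference, so the 5.7 can serve for either. Their SDs agree only at one particular correlation. A power statement built on the SD of one does not carry over to the other without that correlation.

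The outcome matters because it is one of the trial's two primary outcomes. Under the DSMC and interim analyses section, the QoL analysis at 250 patients also decides whether all later patients go to the better of Arms A and B. If the outcome stays open between score and change, two defensible analyses of the same data could lead to different allocation decisions.

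**Working it through.** **Inputs.** From the sample-size section: difference 5.7, SD 15.6, 125 per arm, 80% power, alpha 0.05. From the Randomization section: 1:1 allocation. Assumed, because the document does not say: two-sided test, comparison of means, 15.6 as the SD at a single time, equal SDs at baseline and follow-up. The correlation ρ is unknown, so a range is shown. Power figures use the normal approximation; the t-test figures are within about 0.4 percentage points.

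**Step 1: the plan's own figure.**

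n per arm = 2 × (1.960 + 0.842)² × 15.6² / 5.7² ≈ 118 (119 with the t distribution).

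Power at 125 per arm: the standard error is 15.6 × √(2/125) = 1.973. Then 5.7/1.973 = 2.889, and Φ(2.889 − 1.960) = 82.3% (82.1% with t).

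The stated inputs therefore give slightly more than the claimed 80%. A one-sided 0.05 would need only 93 per arm, so two-sided is the closer reading. The step from 118 to 125 would match an unstated 5% dropout allowance (118/0.95 = 124.2, rounded up to 125) or an allowance for a rank test (118.5 × π/3 ≈ 124).

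**Step 2: change score and adjusted score.**

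SD of a change = 15.6 × √(2(1 − ρ)). This equals 15.6 only at ρ = 0.5.

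Residual SD of the follow-up score after adjustment for baseline = 15.6 × √(1 − ρ²). This never exceeds 15.6.

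| ρ | SD of change | Power, change | n per arm for 80%, change | Adjusted SD | Power, adjusted |
|---|---|---|---|---|---|
| 0.2 | 19.7 | 63% | 189 | 15.3 | 84% |
| 0.3 | 18.5 | 68% | 165 | 14.9 | 86% |
| 0.4 | 17.1 | 75% | 142 | 14.3 | 88% |
| 0.5 | 15.6 | 82% | 118 | 13.5 | 92% |
| 0.6 | 13.9 | 90% | 95 | 12.5 | 95% |

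The follow-up score without adjustment has 82% power at every ρ.

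**Step 3: break-even for the change score.** With 125 per arm, 80% power is reached at an SD of 5.7 / (2.802 × √(2/125)) = 16.08. Setting 15.6 × √(2(1 − ρ)) = 16.08 gives ρ = 1 − (16.08/15.6)²/2 = 0.47. If the 125 already contains a dropout or rank-test allowance, the spare two points of power disappear and the break-even moves to about 0.5.

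**Step 4: if 15.6 is instead the SD of a change.** The single-time SD is then 15.6 / √(2(1 − ρ)). Multiplying by √(1 − ρ²) gives an adjusted SD of 15.6 × √((1 + ρ)/2), which also never exceeds 15.6. With equal SDs, the adjusted analysis keeps at least 82% power on either reading of the 15.6.

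**The case against.** The strongest reply is that there is little real conflict. The change wording appears once, in the Background, right after a study that measured improvement from baseline. The endpoint, sample-size and analysis sections agree with one another, and none of them mentions change. The expected treatment difference is the same either way. That is fair: this is an inconsistency of wording that leaves the SD unclear, and it does not amount to two rival primary endpoints.

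A reader might go further and infer that the second randomization is underpowered. The document does not support that. It gives no correlation, a change score keeps 82% power or more at ρ of 0.5 and above, and the word scores does not exclude an SD of change scores. On the stated inputs, 125 per arm slightly exceeds the claim. If the analysis at 250 patients is not significant, randomization between Arms A and B continues, so 125 per arm need not be the final number.

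It can also be said that covariate adjustment is usually left to the analysis plan. Its absence here is indeed no error. Adjustment is offered because it settles the score-or-change question without depending on the unknown correlation.

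Lastly, the power figures assume a comparison of means, whereas the Primary endpoints section assigns chi-square or Fisher and Farrington-Manning tests to this outcome. Those tests do not fit an outcome sized as a mean difference. That is a separate defect, and replacing the tests would still leave score or change to be decided.

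**Conclusion.** The point holds as an inconsistency with an inexpensive remedy. The Background names a change in EQ-5D-5L, the operative sections name a difference in EQ-5D-5L, and the SD is worded as that of scores.

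Its size is conditional. If 15.6 is a single-time SD, SDs are equal at both times and the test is two-sided at 0.05, the follow-up score has about 82% power. An unadjusted change score would have anything from about 63% (ρ = 0.2) to 90% (ρ = 0.6), with 80% lost only below about 0.47. The baseline-adjusted score has at least 82% at any correlation. If 125 includes an allowance for dropout, that floor is about 80%. No shortfall in power is demonstrated.

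**What to change.** - Use one outcome in the Background, the second-randomization primary endpoint, the sample-size section and the Primary endpoints section: the EQ-5D-5L score at a named primary time point.
- Analyse it as a mean difference between Arms A and B, adjusted for baseline EQ-5D-5L and for sex, the stratification factor of this randomization.
- Confirm from the source data whether 15.6 is the SD of a score at one time or of a change, and label it so. State that the 0.05 is two-sided, if it is, and whether 125 includes an allowance.
- If the sponsor prefers the change score as the outcome, state the SD of the change and recheck the 125 per arm against it.

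The cost is an amendment of wording plus one real decision, the time point, since none is named now. No extra patients are needed. A baseline EQ-5D-5L is implied by the change wording and by the questionnaires prompted before each scheduled visit, but the sponsor should confirm that one is collected before Arm B's intervention starts.

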### Primary endpoints

The primary outcome for the first randomization is HCP-reported toxicity including grade 3-5 adverse events that are possibly, probably, or definitely related to SABR using CTCAE version 5.0. HCP-reported toxicity will be collected at study visits using the AE form. AEs will be compared at the per patient level at any time point post-treatment. Overall rate of AEs is calculated based on the greatest reported severity of SABR-related AEs over the course of the study for each patient. Differences in rates of grade 3 or higher toxicity between groups will be tested using the chi-square test or Fisher’s exact test, as appropriate. Non-inferiority will be assessed using the Farrington-Manning test.

Primary outcome for the 2^nd^ randomization is participant-reported QoL as measured by the EQ-5D-5L. Differences in participant-reported QoL between groups will also be tested using the chi-square test or Fisher’s exact test, as appropriate with non-inferiority assessed using the Farrington-Manning test.

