RT delivery regimens can vary between a single fraction (SF) and multiple fractions (MF) given daily for up to several weeks depending on the location of metastases, while SABR is generally limited to eight or fewer fractions. MF RT is administered to reduce the radiation load given at a single event, which may reduce late toxicities. However, SF RT may be more cost effective and reduces patient treatment time. While SF SABR is a safe and effective treatment for brain metastases, the toxicity profile for other metastatic sites and in the setting of oligometastases is not well established. One study comparing SF with MF SABR in treatment of 1-3 pulmonary oligometastases showed no statistically significant difference in toxicities or OS between the groups, however, this was a retrospective study and limited to a small sample size [9]. The recent randomized phase 2 SAFRON II trial reported no difference between SF and MF SABR for lung oligometastases in the primary endpoint of severe toxicity, and also similar local control, survival and qualify-of-life (QoL) between treatment arms [10, 11]. Another recently completed phase III randomized controlled trial (RCT) comparing local control of oligometastases between SF and MF SABR found significantly lower cumulative incidence of local recurrence in the SF arm [12]. However, the biologically equivalent dose for the MF arm was significantly lower than for the SF arm, thereby limiting the study’s interpretation and generalizability. We have found no studies that have investigated SF vs. MF for oligoprogression. Consensus among radiation oncologists and our patient partners was to perform a study with toxicity as the primary outcome given concerns that SF SABR may have a higher rate of toxicity to nearby organs at risk. It is critical that a properly powered phase III trial is conducted comparing toxicity, efficacy, and cost-effectiveness between SF and MF SABR with similar biologically effective doses, a larger sample size, and inclusive of all tumour sites to expand our knowledge of SABR in both oligometastatic and oligoprogressive settings and to guide evidence-based prescription of SF SABR.

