### 1st randomization

#### Primary endpoint

##### Toxicity

◦ Defined as grade 3-5 adverse events (Common Terminology Criteria for Adverse Events [CTCAE] version 5.0) that are possibly, probably, or definitely related to SABR.

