## Study design

This is a phase III, investigator-led, open-label, multi-institutional, RCT using a 2x2 factorial design with two randomizations and two primary outcomes. Participating institutions will be tertiary, academic hospitals or RT treatment institutions in Canada, the United Kingdom, United States, and Australia (updated country list available on ClinicalTrials.gov entry NCT05784428). The first and primary randomization is by dose and fractionation, while the second randomization is by HCP-led intervention based on PRO symptom screen, as displayed in schema Fig. 1.

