### Data Safety Monitoring Committee (DSMC) and interim analyses

There will be four interim analyses. The DSMC will conduct the first interim analysis once 50 patients are accrued. For this analysis, the DSMC will be blinded to the identity of each treatment arm, but OS and toxicity data will be presented for each arm (Arm 1 and 2), and treatment doses and volumes will be presented for SAEs reviewed. There are three planned interim analyses for efficacy in addition to the final analysis. The first two interim analyses are expected to be carried out when the total number of observed study deaths reaches 50 and 100, thus treatment details will be reviewed to determine plausible causation of toxicities. As such, interim efficacy analyses will not be blinded. The DSMC will recommend stopping the trial if there is an OS difference that is statistically significant with a threshold of p < 0.001 using the stratified log-rank test. The third interim analysis will be carried out after 50% accrual, or 250 patients to review QoL for Arm A and B. If the analysis yields significant results, we will select the superior arm and assign all patients moving forward to that group for the remainder of the trial duration. However, if results are not significant, we will continue to randomize patients to either Arm A or B until study completion. This will not affect the 1st randomization between Arms 1 and 2.The final analysis is expected to be carried out 3 years after the enrollment of the last subject.

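### The primary toxicity endpoint counts only events that HCPs in an open-label trial attribute to SABR, and at about 15 events per arm a shift of a few attributions can decide non-inferiority

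*Protocol article*

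**What the plan says.** The endpoint list (1st randomization, Toxicity) restricts the primary endpoint to grade 3-5 events "that are possibly, probably, or definitely related to SABR". The Sample size calculation section uses the same restriction, and the Primary endpoints section words the outcome as "HCP-reported toxicity including grade 3-5 adverse events that are possibly, probably, or definitely related to SABR using CTCAE version 5.0".

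On the source of the data, Primary endpoints states: "HCP-reported toxicity will be collected at study visits using the AE form". The per-patient rate is "calculated based on the greatest reported severity of SABR-related AEs over the course of the study for each patient". The chi-square or Fisher test and the Farrington-Manning non-inferiority test are both applied to that rate.

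On masking, Study design says: "This is a phase III, investigator-led, open-label, multi-institutional, RCT using a 2x2 factorial design with two randomizations and two primary outcomes". The article describes no masked assessor of relatedness.

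The Background explains that toxicity was made the primary outcome "given concerns that SF SABR may have a higher rate of toxicity to nearby organs at risk".

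**The concern.** A grade 3-5 event judged unrelated never enters the primary comparison. The dividing line lies between unrelated and possibly related, which is the most discretionary point of the scale. These patients have metastatic cancer, may be continuing systemic therapy, and are counted for events at any time after treatment, so competing explanations will be common.

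If the same clinical event is attributed differently according to arm, the observed difference mixes toxicity with attribution. Reading SF events as due to disease or drugs makes a false non-inferiority claim more likely. Reading them as due to SABR because one large fraction is thought risky makes a true claim harder to reach. Because both primary tests rest on the same filtered events, neither would reveal such a shift.

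**Working it through.** **Inputs.** From Sample size calculation: 299 per arm, reference rate 5%, margin 5 points, SF rate 10% under the null and 5% for power, one-sided alpha 0.025, unpooled z test. From Primary endpoints: the Farrington-Manning test. The size of any attribution shift is my assumption, because the article gives none.

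**The plan's own figure.** n = (1.960 + 0.842)² × (0.05 × 0.95 + 0.05 × 0.95) / 0.05² = 298.3, so 299 per arm. Unpooled z power at 299 is 80.1%. The stated size reproduces.

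**Expected counts.** 5% × 299 ≈ 15 patients with an event per arm. The 5-point margin is also about 15 patients.

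**Where the decision turns.** The Farrington-Manning statistic is z = (p_SF − p_MF − 0.05) / √{[a(1−a) + b(1−b)]/299}. Here a and b are the maximum-likelihood rates restricted to b = a + 0.05. With 15 MF patients affected:

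| SF patients | z | one-sided p | result |
|---|---|---|---|
| 15 | | 0.0048 | non-inferior |
| 18 | −2.03 | 0.0214 | non-inferior |
| 19 | −1.84 | 0.0326 | not shown |

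Four extra attributed SF patients overturn an equal 15 v 15 result. At the boundary, one patient decides.

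**Effect of an assumed shift.** The probability of declaring non-inferiority is summed exactly over the two binomial distributions, with the recorded MF rate at 5%.

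| True SF rate | Assumed shift in SF | Recorded SF rate | P(declare non-inferiority) |
|---|---|---|---|
| 10% | none | 10% | 2.4% |
| 10% | 10% of events called unrelated | 9% | 6.6% |
| 10% | 20% of events called unrelated | 8% | 15.6% |
| 5% | none | 5% | 76.7% |
| 5% | 3 patients over-attributed | 5% + 3/299 = 6.0% | 53.7% |

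At a true 10%, the 10% and 20% shifts are about 3 and 6 patients of 299 (0.01 × 299 and 0.02 × 299). The one-patient step is 2.4% to 3.4% for the false claim and 76.7% to 69.5% for power.

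**Would attribution-free analyses show it?** I simulated the 20% shift (true rates 10% v 5%) with an assumed background rate of unrelated grade 3-5 events between 1% and 20%. The attributed endpoint gives a false claim in about 15.6% of trials. The attributed and all-cause Farrington-Manning tests both exclude the margin in only about 2 to 2.5%. Most false claims would therefore appear as discordant results.

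**Price of the added noise.** The 95% half-width is 1.96 × √[2q(1−q)/299], which is 4.8 points at an all-cause rate q of 10% and 6.4 points at 20%. With equal arms, the same exact sum gives the all-cause test a chance of excluding the margin of about 52% at 10% and 33% at 20%.

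**The case against.** The strongest reply is that the endpoint is worded consistently throughout the article, and that adjudication procedures, sensitivity analyses and form content usually sit in the full protocol or the SAP, neither of which is shown. That stands as far as it goes: their absence from the article is not the point here. The point is the choice the article does fix, namely HCP attribution as the filter on the only events that both primary tests use.

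Three stronger readings are tempting, and the document does not support them.

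- A reader might infer that radiation oncologists expect SF to be more toxic. The Background records only that it may be. The same section cites a randomized phase 2 trial in lung oligometastases with no difference in severe toxicity.
- A reader might infer that relatedness is decided by a committee that can see the treatment, because the DSMC section says that "thus treatment details will be reviewed to determine plausible causation of toxicities". That is interim monitoring. Nothing there assigns the endpoint, and the first interim review is blinded to arm identity.
- A reader might infer a known bias towards false non-inferiority. The only stated concern, about SF toxicity, points if anything to over-attribution in SF, which works against the claim. The inclusive threshold of possibly related also limits under-counting. The direction is unknown.

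It is also fair that the article gives no attribution rules at all, so nothing can be said about how evenly they would be applied. CTCAE grading is a further judgement made with knowledge of the arm, and removing the attribution filter does not address it.

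**Conclusion.** The concern holds as a sensitivity of the fixed primary endpoint, not as evidence of bias. At the design rates the decision turns on one to four attributed patients. A differential of three patients, about 1% of an arm, raises false non-inferiority from 2.4% to 6.6% or lowers power from 77% to 54%, depending on direction. Missing 20% of SF events at the null rate gives about 15.6%.

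This rests on three assumptions: that HCPs know the arm, which is inferred from open-label status and the absence of any described masking; that the shift affects SF only; and that its size lies in the range shown. The change should be made because it is inexpensive and bears on the trial's main conclusion, but it does not invalidate the design.

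**What to change.** Keep the HCP-attributed endpoint primary. Add to Primary endpoints two supportive analyses using the same Farrington-Manning test and 5-point margin, reported with confidence intervals beside the primary result:

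1. All grade 3-5 AEs, regardless of attribution.
2. Grade 3-5 AEs in a pre-defined body region of any SABR-treated lesion, counted whatever relatedness was assigned. This should include lesions treated later under the section on further RT at new metastatic sites.

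State that the AE form records every grade 3-5 AE with its relatedness category. If the primary test succeeds but a supportive analysis does not also exclude the margin, report that non-inferiority rests on HCP attribution.

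Do not make the claim conditional on the supportive point estimates lying below 5 points. At the null the true all-cause difference is itself close to 5 points, so such a rule barely discriminates. Under the 20% shift it lowers false claims only from about 15.6% to about 13-15%, and it cannot restore power lost to over-attribution.

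The cost is wording, definition of the body regions, mapping of events to them, and some programming, with no extra visits. The downside is noise from unrelated events, which grows with their background rate: a supportive analysis may fail to exclude the margin even when SF is truly non-inferior. That is why both stay supportive, and why a failure should be read as disclosure and not as evidence of harm.

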## Statistical considerations

### Randomization

#### 1^st^ randomization

The study will employ a 1:1 randomization between Arm 1 and Arm 2, with further stratification between 1) systemic therapy within last two weeks (yes vs. no), 2) number of sites to be treated with SABR (one vs. multiple) and 3) SABR to abdominal sites (yes vs. no).

Permuted block randomization will be used to reduce selection bias, promote allocation concealment, and improve balance across groups over the trial period. Patients will be randomized based on a permuted block design using a block size based on a multiple of 3 (with block size known only to statistician until analysis is completed [23]. The Coordinating Centre and trial statistician will be responsible for configuring the module within REDCap, the electronic data capture (EDC) system that will be used to randomize participants.

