### Survival and secondary endpoints

PFS and OS will be calculated using the Kaplan-Meier method with differences compared using the stratified log-rank test. Pre-planned subgroup analysis will occur based on the stratification factors, and also based on the use of immunotherapy vs. non-immunotherapy systemic agents. A multivariable Cox proportional hazards regression analysis will be used to determine baseline factors predictive of survival endpoints. For the endpoint of time to new metastases, a Fine and Gray competing risk analysis will be used to account for competing risk of death from any cause.

LCR will be calculated using the cumulative incidence function including mortality as competing risk.

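### The primary toxicity comparison omits the three factors that stratify the randomization (a small, conservative loss of power), and its any-time crude rate needs a sensitivity analysis for patients lost to follow-up

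*Protocol article*

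**What the plan says.** **Endpoint.** The protocol article, under Toxicity (1st randomization), gives the primary endpoint: "Defined as grade 3-5 adverse events (Common Terminology Criteria for Adverse Events [CTCAE] version 5.0) that are possibly, probably, or definitely related to SABR". Under Primary endpoints, "AEs will be compared at the per patient level at any time point post-treatment", and the overall rate is "calculated based on the greatest reported severity of SABR-related AEs over the course of the study for each patient". Ascertainment is by visit: "HCP-reported toxicity will be collected at study visits using the AE form".

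**Test.** "Differences in rates of grade 3 or higher toxicity between groups will be tested using the chi-square test or" Fisher's exact test. Non-inferiority is assessed with the Farrington-Manning test. No stratification is mentioned for any of them.

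**Randomization.** Allocation is 1:1 "with further stratification between 1) systemic therapy within last two weeks (yes vs. no"), then by one versus multiple SABR sites and by whether abdominal sites are treated. That makes three binary factors and eight strata.

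**Elsewhere in the same plan.** Under Survival and secondary endpoints, PFS and OS have "differences compared using the stratified log-rank test", and lesional control uses a cumulative incidence function with death as a competing risk.

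**Loss to follow-up.** The article states no analysis set, denominator or loss rule for toxicity. The section on discontinuation and withdrawal asks that end-of-study evaluations be obtained from patients who stop, and allows replacement at the study principal investigator's discretion.

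**The concern.** The three factors were presumably chosen because they bear on toxicity risk. When the randomization balances such factors and the analysis leaves them out, the estimated standard error includes between-stratum variation that the design has already removed. The plan accounts for this in its survival tests but not in the test that decides the trial.

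The second matter is the any-time, worst-grade rate. A patient who stops attending before any event has no later grade to report. If that patient stays in the denominator, the effect is the same as scoring a non-event. In a non-inferiority comparison on an absolute scale, events missed in both arms shrink the difference while the 5-point margin stays put. What is at stake is a little power in the first case and, under some loss patterns, the false non-inferiority rate in the second.

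**Working it through.** **Inputs from the protocol (Sample size calculation, 1st randomization):** 299 per arm; reference rate 5%; single-fraction rate 10% under the null and 5% for power; margin 5 points; one-sided alpha 0.025; unpooled z test.

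**Step 1: the plan's own figure.** n per arm = (1.960 + 0.842)² × (0.05×0.95 + 0.05×0.95) / 0.05² = 298.3, rounded up to 299. Power at 299 is 80.1%. The plan's figure reproduces.

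**Step 2: cost of omitting the strata.** The documents give no stratum shares or risks, so these are assumptions. Take 30% of patients with abdominal SABR, toxicity *pa* there and *pn* elsewhere, and 0.3·pa + 0.7·pn = 0.05. The within-stratum variance is 0.3·pa(1−pa) + 0.7·pn(1−pn), against 0.05×0.95 = 0.0475 unstratified. Stratified power is Φ(0.05·√(299/(2·variance)) − 1.960).

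| pa | pn | Within-stratum variance | Ratio to 0.0475 | Power, stratified |
|---|---|---|---|---|
| 10% | 2.9% | 0.0464 | 0.977 | 81.0% |
| 12% | 2.0% | 0.0454 | 0.956 | 81.8% |
| 15% | 0.7% | 0.0432 | 0.910 | 83.7% |

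Against the design's 80.1%, the gain is about 1 to 4 points. The top figure is generous, because with stratified allocation the unstratified test also beats its nominal power. For the last row that is Φ((0.05·√299 − 1.960·√0.0950)/√0.0864) = 81.2%, so the like-for-like gain is 83.7 − 81.2 = 2.5 points.

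A second scenario uses all eight strata, with risk ratios of 1.5 (systemic therapy), 1.5 (multiple sites) and 3 (abdominal), the first two factors split evenly and 30% abdominal. Power is 80.4% unstratified and 81.0% stratified.

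**Step 3: direction.** In that eight-stratum scenario, at true rates of 10% and 5%, the unstratified test's type I error is 0.023 to 0.024, against 0.025 stratified. Omitting the factors makes non-inferiority slightly harder to claim.

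**Step 4: missed events.** Suppose a share *f* of events goes unseen and the patients stay in the denominator. Observed rates are then (1−f) times the true rates. At true 10% versus 5% with f = 20% in both arms, these are 8% and 4%: an apparent difference of 4 points against a margin of 5. Exact binomial enumeration of the Farrington-Manning test at 299 per arm gives:

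| Events missed, SF / MF | Apparent difference (points) | False non-inferiority |
|---|---|---|
| 0 / 0 | 5.0 | 0.024 |
| 10% / 10% | 4.5 | 0.041 |
| 20% / 20% | 4.0 | 0.069 |
| 20% / 10% | 3.5 | 0.107 |
| 10% / 20% | 5.0 | 0.024 |
| 0 / 20% | 6.0 | 0.007 |

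The documents give no loss rate, so every *f* above 0 is assumed.

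**The case against.** **On stratification.** The gain is small and the omission is conservative. The top of the power range needs 15% against 0.7%, roughly a 21-fold contrast. If both arms run at 5%, only about 0.05 × 598 = 30 events are expected over eight strata, so a simple test is defensible, and covariate adjustment is often left to the SAP. The modest size stands. But the article names its primary tests and specifies stratification for PFS and OS, so a SAP that follows the text would run the primary test unstratified. The sparse strata call for a collapsing rule, not for dropping the factors.

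**On losses.** A reader might infer that the plan scores patients lost early as free of toxicity and so biases the trial towards non-inferiority. The documents do not support that. No denominator or loss rule is stated, and a SAP may set one. End-of-study evaluations are requested at discontinuation. A patient lost after a recorded event still counts, so losing 10% of patients is not the same as missing 10% of events. Direction depends on which arm loses more. A patient who dies without toxicity is properly a non-event when death is a competing event. All of this stands and makes the point conditional.

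**On a fixed horizon.** Replacing the any-time endpoint with a truncated one would drop late toxicity, which the Background gives as a reason for fractionating, and would lower both rates against the same margin. This stands too: the fixed horizon belongs in a sensitivity analysis.

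**Conclusion.** The concern holds in a limited form. The stated primary toxicity comparison is unstratified, although three factors stratify the randomization and the PFS and OS tests are stratified. The standard error is slightly too large, and the cost runs from under 1 to about 4 points of power. The upper end rests on an extreme assumed contrast and on comparison with nominal design power. It would be wrong to read this omission as favouring non-inferiority.

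The exposure to missed events is conditional. It arises only if patients lost before any event stay in the denominator. With equal loss in both arms, false non-inferiority rises from 2.4% to 4.1% with 10% of events missed, and to 6.9% with 20%. The rise is larger if the single-fraction arm loses more. It disappears or reverses if loss is sufficiently higher in the multi-fraction arm. That justifies a required sensitivity analysis, not a change of primary endpoint.

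**What to change.** 1. Make the primary non-inferiority test a stratified risk difference over the three randomization factors: stratified Miettinen-Nurminen (the stratified counterpart of Farrington-Manning) or Mantel-Haenszel. Compare the upper 97.5% confidence limit with 5 points.
2. Fix in advance, before arm-level data are seen, the rule and order for collapsing sparse strata.
3. Keep the any-time, worst-grade endpoint as primary.
4. Add a required sensitivity analysis: cumulative incidence of SABR-related grade 3-5 toxicity by arm at a horizon every patient can reach. Since the final analysis is planned 3 years after the last enrolment, that means up to 3 years. Treat death as a competing event and censor loss to follow-up.

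The cost is protocol or SAP wording and minor extra programming, with no added patients or visits. The downsides are that some strata may need collapsing, and that the sensitivity analysis does not cover events beyond its horizon, which the primary analysis still counts.
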